#### Psychological variables related to physical activity

Psychological variables were measured to determine their potential mediating effect. Specifically, intention to perform physical activity was assessed using three items [47], which asked participants to rate their level of intention to perform physical activity (e.g. "I intend to take part in regular physical activity most days (at least five) of the next week."). The items were scored using a seven point Likert scale ranging from -3 (completely disagree) to 3 (completely agree). A mean score from the three items is used to give an overall measure of intention.

Physical activity task efficacy was assessed using nine items adapted from the Self Efficacy Scale [48]. Participants were asked to rate their level of confidence to perform physical activity at increasing intensity levels and increasing amounts of time most days of the week. Durations used were 10 minutes, 30 minutes and 60 minutes and intensities were labeled as light, moderate and hard. Participants were provided with descriptions of the intensity levels and examples of types of physical activities at each level. Participants rated their confidence levels on a scale ranging from 0% (I am not confident at all) to 100% (I am completely confident). Scores from these items are summed, and divided by nine to give a mean score for task efficacy. Greater scores indicate greater efficacy to perform physical activity at harder intensities for longer periods of time.

Physical activity barrier efficacy was assessed with six items adapted from the Barriers Efficacy Scale [48]. Items assessed the level of perceived confidence of the participant to perform regular physical activity in the face of a particular barrier (e.g. "If it is bad weather"). Participants rated their confidence levels on a scale ranging from 0% (I am not confident at all) to 100% (I am completely confident). Scores from these items are summed, and divided by six to give a mean score for barrier efficacy. Greater scores indicate greater efficacy to perform physical activity in the face of a variety of barriers.

Perceived competence for physical activity was assessed using the athletic competence six item subscale of the Self-Perception Profile for Children [49]. The participant is provided with two statements and asked to decide which one they are more like (e.g., "Some children do well at sports" vs. "Other children don't do so well"). After deciding between the two alternatives, the participant then decides if the statement is "really true for me" or "sort of true for me". Items are scored on a four point scale, with higher scores indicating more positive self-perceptions. Scores are summed then averaged.

Perceived enjoyment of physical activity was assessed using the 14 item Physical Activity Enjoyment Scale [50], adapted for use in adolescents in 2001 [51]. Participants rate their agreement with statements (e.g., "When I am active I enjoy it") on a five point Likert scale. Scores are summed, with higher scores indicating a higher level of enjoyment.

#### Video game use

During the seven days following each assessment participants completed a daily log detailing the time spent playing video games. A distinction was made between active video games (e.g. EyeToy) and traditional non-active video games (e.g. Xbox). The video game log was pre-tested in the eGAME pilot study [33].

#### Snack food consumption

During the seven days following each assessment participants completed a record of snack foods consumed, which were defined as "something you eat between your main meals (breakfast, lunch and dinner)". The snack food record consisted of pictures of 29 common categories of snack foods and drinks (e.g., pizza, fruit, muesli bars, milk, water etc.). For each food or drink, three pictures were presented showing different snack serving sizes. For example, for the fruit category, the three pictures showed half an apple, a whole apple, and two apples. Participants indicated the number of servings of the respective food and serving size they had consumed on each week day. Each serving size was assigned a caloric value (kJ). The caloric value of all reported snacks is added and then divided by seven days to give average daily total energy consumed from snacks (kJ). The snack food log was developed and pre-tested prior to the study.

### Outcomes

The primary outcome is change in BMI (kg/m^2^, z-score and centile) from baseline to 12 and 24 weeks. The secondary outcomes are change from baseline to 12 and 24 weeks on the following measures: Percent body fat (%), waist circumference (cm), physical fitness measured in VO_2max _(ml/kg/min), PAQ-C score, average daily time spent in light to vigorous activities (minutes), average daily time spent in active video games (minutes) and average daily time spent in non-active video games (minutes). Additional tertiary outcomes include change from baseline to 12 and 24 weeks on the following measures: Average daily time spent in light activities (minutes), moderate activities (minutes) and vigorous activities (minutes); psychological variables intention, self-efficacy, barrier efficacy, perceived competence, perceived enjoyment; and average daily total energy consumed from snacks (kJ).

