### Design

The eGAME study is a standard two-arm parallel RCT. Eligible children are randomized to either an active video games intervention or control (no change) following baseline assessment. The randomization is via a computerized central randomization service and stratified by sex and ethnicity. The study manager and research assistants are responsible for enrolling participants and group assignment. Ethical approval for the study was granted by the Northern Y Ethics Committee (reference: NTY/07/09/099).

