### Sample size

A sample size of 330 participants was estimated to provide at least 90% power at 5% level of significance (two-sided) to detect a 0.8 kg/m^2 ^difference in change in BMI from baseline to the end of intervention period between the two groups, assuming a standard deviation (SD) of 2.0 kg/m^2 ^and allowing for 20% loss to follow up. The estimated difference in BMI assumed a difference in weight between groups at the end of intervention of approximately 2 kg with an average height of 1.58 m. This sample size also provides at least 90% power to detect an estimated 3–5 ml/kg/min difference in peak VO_2max _assuming a SD of 7 ml/kg/min. Recruitment of equal numbers of Māori (indigenous people) (n = 110), Pacific, (n = 110) and non-Māori/non-Pacific (n = 110) participants would provide nearly 80% power for the sub-group analysis under the same assumptions.

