### Statistical analysis

Statistical analyses will be performed using SAS version 9.1.3 (SAS Institute Inc. Cary NC) and R version 2.8.1 (R Foundations for Statistical Computing). All statistical tests will be two-tailed and a 5% significance level maintained throughout the analyses. All treatment evaluations will be performed on the principle of Intention to Treat (ITT). Repeated measures analysis using the mixed model will be carried out to evaluate the effect of intervention on change from baseline measures at 12 and 24 weeks, adjusting for baseline outcome measure, age (in years), sex (male/female), and ethnicity (Māori/Pacific/nMnP). With roughly equal number of Māori, Pacific and non-Māori non-Pacific participants, appropriate sub-group analysis will be carried out for each ethnicity if there is a significant overall treatment effect.

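### The primary outcome spans three BMI scales and two visits with no deciding comparison named, all tests run at an unadjusted 5%, and the sample size covers only one of the six

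*Protocol article*

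**What the plan says.** Three sections of the protocol article bear on this.

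- **Outcomes:** "The primary outcome is change in BMI (kg/m^2^, z-score and centile) from baseline to 12 and 24 weeks". Three scales at two visits share primary status, with no order among them.
- **Statistical analysis:** "All statistical tests will be two-tailed and a 5% significance level maintained throughout the analyses". The planned model is a repeated-measures mixed model covering both follow-up visits, adjusted for baseline value, age, sex and ethnicity. The section does not say whether the primary test is the 12-week contrast, the 24-week contrast or an effect over both visits. It adds that "appropriate sub-group analysis will be carried out for each ethnicity if there is a significant overall treatment effect", without naming a scale or visit for that effect.
- **Sample size:** 330 participants for 90% power with a two-sided 5% test, to detect a 0.8 kg/m² "difference in change in BMI from baseline to the end of intervention period between the two groups", with an SD of 2.0 kg/m² "and allowing for 20% loss to follow up".

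The Background section gives a six-month intervention and the Procedure section places the last assessment at 24 weeks. The end of the intervention in the sample-size statement is therefore the 24-week visit.

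**The concern.** The three sections do not describe the same primary question. One gives primary status to six quantities, one tests everything at full 5%, and one sizes the trial for a single quantity. A reader of the eventual report could not tell from this text which result was meant to decide.

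Two things are at stake. First, if a significant result on any scale at either visit were taken as success, the chance of a false claim under no effect would exceed 5%. Second, the 90% power statement describes one of the six comparisons and not the primary outcome as defined.

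The condition for the ethnic sub-group analyses has a related weakness. It depends on an overall effect that is not tied to any particular test, so whether it is met could be decided after the results are seen.

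**Working it through.** **Inputs from the protocol article.** Difference 0.8 kg/m², SD 2.0 kg/m², two-sided 5%, power 90%, loss 20% (Sample size); two parallel arms (Design); three scales and two visits (Outcomes). Assumed, because not stated: 1:1 allocation and all correlations below.

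**1. Reproduce the stated sample size.**

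n per arm = 2 × SD² × (z₀.₉₇₅ + z₀.₉₀)² / δ² = 2 × 4 × (1.960 + 1.282)² / 0.64 ≈ 131.3, rounded up to 132.

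Total evaluable 2 × 132 = 264; allowing for 20% loss, 264 / 0.8 = 330. This matches the plan exactly.

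Power at 132 per arm: 0.8 / (2.0 × √(2/132)) = 3.25, and Φ(3.25 − 1.96) = 90.1%.

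The figure therefore belongs to one test, on one scale, at one time, with the whole 5%.

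**2. Count the comparisons.** 3 scales × 2 visits = 6. If the repeated-measures model is used for one overall test per scale, there are 3. If one scale is tested at both visits, there are 2.

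**3. Chance of at least one false positive when any result counts.** With independent tests the figure for six is 1 − 0.95⁶ = 26.5%. The tests are in fact strongly related, so correlated normal statistics were simulated (2,000,000 draws, each |z| compared with 1.96). For six tests, the correlation matrix was the product of a between-scale and a between-visit correlation.

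| Reading | Assumed correlation | Any false positive |
|---|---|---|
| Six tests | scales 0.80, visits 0.5 to 0.8 | 17.3% to 14.9% |
| Six tests | scales 0.90, visits 0.5 to 0.8 | 14.9% to 12.8% |
| Six tests | scales 0.95, visits 0.5 to 0.8 | 13.1% to 11.3% |
| Six tests, wide grid | scales 0.5 to 0.98, visits 0.3 to 0.9 | 22.9% to 9.0% |
| Three scales, one test each | scales 0.80, 0.90, 0.95 | 9.8%, 8.4%, 7.3% |
| One scale, two visits | visits 0.5 to 0.8 | 9.0% to 7.8% |
| kg/m² at 24 weeks only | none needed | 5% |

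**4. Cost of adjusting instead of choosing.** Bonferroni over six tests sets each at 0.05 / 6 = 0.0083. For the same 0.8 kg/m² difference, power at 132 per arm falls from 90.1% to 73.0%. Restoring 90% needs 386 evaluable participants, or 386 / 0.8 = 482.5, rounded up to 483 recruited. Over three tests, power is 80.4% (423 recruited for 90%). Over two, it is 84.3% (390 recruited). Bonferroni is conservative for tests this closely correlated, so these are upper limits on the cost.

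**The case against.** The strongest defence is that the article names one primary outcome, BMI change, and merely lists the scales and visits on which it will be reported. Four parts of that defence stand.

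- A reader might infer six co-primary tests. The document does not use that term. Strictly, co-primary endpoints must all succeed, which does not inflate the type I error. The inflation above needs a rule that any one result suffices, and no such rule is stated.
- A reader might take a figure such as 12–17% as the trial's false-positive rate. It cannot be derived from the documents. It depends on assumed correlations and on the any-of-six reading, and other readings of the same text give anything from 5% upward.
- A reader might conclude that the trial has no primary target at all. The Sample size section points clearly to kg/m² at the end of the intervention, and sizing a trial on one scale is not itself an error.
- A reader might say that the primary outcome gates the sub-group analyses. The text says only that an overall effect must be significant, and overall may simply mean the whole sample as against one ethnic group. The wording is loose, but that dependence is not shown.

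It can also be said that the choice of model contrast is commonly left to the statistical analysis plan, which is not shown and may settle it. That is fair for the contrast alone. It does not answer the main point: this article itself defines the primary outcome, defines it in the plural, and sets it beside a blanket 5% level and a sample size for one comparison. That is a mismatch within the document, not an absent detail.

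**Conclusion.** The point holds as an unreconciled definition of the primary outcome. Up to six comparisons carry primary status, none is named as decisive, 5% is applied to each without adjustment, and the 90% power statement is valid for only one of them (330 in total, 90.1% power reproduced).

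How far the error rate could rise depends on the decision rule and on correlations that the documents do not give. If any of the six could count, it would be about 11–17% for between-scale correlations of 0.80–0.95 and between-visit correlations of 0.5–0.8, and about 9–23% over the wider grid. With two or three tests it would be about 7–10%. With a single named test it is 5%. The documents do not support saying that the trial has any particular inflated rate; they support saying that the text does not secure 5%.

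**What to change.** Name one primary test: change in BMI (kg/m²) from baseline to 24 weeks, estimated as the 24-week treatment contrast in the planned repeated-measures mixed model, at two-sided 5%. Make the z-score and centile results, and all 12-week results, secondary or supportive. Tie the condition for the ethnic sub-group analyses to that one test.

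This brings the Outcomes and Statistical analysis sections into line with the Sample size section. It leaves 330 participants and the 90% power statement valid and needs no division of the 5% level.

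The cost is a wording change in the protocol and analysis plan, recorded before any outcome comparison between the groups is run, and the loss of alternative routes to a positive primary result.

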## Methods/Design

### Feasibility studies

The main eGAME study followed a three phase feasibility study conducted in 2005/2006. Phase one consisted of focus groups with children and adults to determine attitudes and preferences to video game play. All children enjoyed active video games, however older children (14 years) preferred traditional non-active games. Adults preferred that children performed physical activity in more traditional outdoor activities but said they would prefer active video game play to the non-active video games. For phase two a laboratory study was conducted to quantify the energy expenditure associated with playing active (Sony EyeToy^®^) and non-active video games [32]. Overall, results showed that energy expenditure was significantly greater in the active video games compared to rest and non-active gaming conditions. The exercise intensity of the active video games ranged between 3.2 and 6.8 child-specific METs.

In phase three a pilot randomized controlled trial (RCT) was conducted to determine the effect of active video game play on physical activity levels [33]. Twenty children aged 10–14 years were randomly assigned to either receive an active video game intervention (n = 10), or no change (control; n = 10). Over the 12 week intervention period, the average time spent in all physical activities (measured by accelerometry) was higher in the active video game intervention group compared to the control group.

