### Participants

Children aged 10–14 years living in the greater metropolitan Auckland area, who are overweight (according to the Cole international cut-offs for child obesity) [37], play ≥ two hours of video games per week, and have no contraindications to perform physical activity are eligible to participate in the study. Participants are required to own a PlayStation^® ^2 or 3 gaming console but not the EyeToy™ or Dance Mat technology. Only one child per household is eligible to take part.

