**Figure 1 F1:**
[figure not shown]
**Example of child playing Sony EyeToy™ active video game**. Reproduced with permission from Sony Computer Entertainment Europe.

Current physical activity recommendations for children and adolescents are to perform 60-minutes of moderate to vigorous physical activity on most days of the week [38]. In the eGAME study, children were encouraged to meet these recommendations by (1) supplementing periods of inactivity with active video game play; and (2) to substitute periods of traditional inactive video game play with the active version. As compliance with the intervention has been highlighted as an issue in previous active gaming research, several reinforcement strategies were used to maximize compliance in this study. Firstly, the introduction of new games to participants was staggered to maintain interest and motivation (games were given at baseline and again at 12 weeks). Second, intervention participants were reminded at their follow-up assessments to continue playing the games. Children in the control group were asked to continue their normal video game playing and physical activity behavior. At the end of the study, the control group received the active video games upgrade package.

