#### Objectively-measured physical activity

Accelerometry was used to assess objectively-measured physical activity. The Actigraph (Model AM7164-2.2C) uniaxial (single-horizontal plane) accelerometer was used, which measures motion in the vertical plane, with movement outside of 'normal' motion being filtered electronically. Piezo-electric transducers and microprocessors detect movement which is converted to digital signals (movement counts).

Participants wore the accelerometer for seven consecutive days following each assessment. They were instructed to wear the monitor on their right hip in the mid-axilla line, during waking hours. Exceptions to this were any activities involving water (water sports, showering etc.), and any contact sports, in which wearing the accelerometer may cause injury to the participant, or damage the monitor. Participants also completed a daily log detailing the time the monitor was first put on and removed.

Because children tend to engage in physical activity in short duration bursts, a 10 second epoch was used and summed to give an activity count per minute [44]. The following cut-off points for METS were used to define light, moderate and vigorous levels of physical activity using the accelerometer: Light = 1.5 – 2.9 METS, moderate = 3 – 5.9 METS, vigorous ≥ 6 METS. For each valid recorded minute, the following equation was used to convert activity counts into equivalent MET values: MET = 2.757 + (0.0015*counts/min) - (0.08957*age) - (0.000038*counts/min*age) [45]. The obtained MET value was then converted into corresponding level of physical activity using the defined cut-off points. A valid accelerometer minute was defined as a recorded minute that does not fall into a sequence of ≥ 20 minutes of missing activity counts. A valid accelerometer day was defined as a recorded day that has a minimum of 600 valid minutes (i.e. 10 hours) [46]. All non-valid days and minutes will be removed from the accelerometer data before analysis. The average daily time spent in light/moderate/vigorous activities is calculated from valid minutes in valid days at each visit (a maximum of 7 days).

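### The only accelerometer secondary outcome pools light with moderate and vigorous minutes and, on the protocol's own MET equation, is close to valid wear time

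*Protocol article*

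**What the plan says.** All references are to the protocol article.

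- **Outcomes, secondary:** the one accelerometer measure is "average daily time spent in light to vigorous activities (minutes". The other secondary measures of activity behaviour are the PAQ-C score and game time from the log, both self-reported. VO2max is a fitness measure.
- **Outcomes, tertiary:** "Average daily time spent in light activities (minutes), moderate activities (minutes) and vigorous activities (minutes", each as its own outcome. Combined moderate and vigorous time appears at no level.
- **Objectively-measured physical activity:** the bands are "Light = 1.5 – 2.9 METS, moderate = 3 – 5.9 METS, vigorous ≥ 6 METS". Counts are converted minute by minute with "MET = 2.757 + (0.0015*counts/min) - (0.08957*age) - (0.000038*counts/min*age". Averages use valid minutes in valid days.
- **Intervention:** children were encouraged towards the recommendation to "perform 60-minutes of moderate to vigorous physical activity on most days of the week", by adding active play to inactive periods and by replacing inactive video games with active ones. The Discussion section on less healthy behaviours repeats that replacement.
- **Feasibility studies:** "The exercise intensity of the active video games ranged between 3.2 and 6.8 child-specific METs".

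**The concern.** The intervention is meant to turn sitting at a console into movement of moderate or vigorous intensity. The one objective activity outcome above tertiary rank should respond to that change. A sum that includes light minutes responds only if the minutes given up were previously outside the sum. Whether they were depends on where the equation places a child who is sitting still.

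If sitting still already falls in the light band, the outcome adds up nearly all valid time and says little about activity. A null result on it could not be read as no effect on physical activity. A positive result could reflect longer monitor wear in one arm. In a trial whose participants and assessors know the allocation, the self-reported secondary measures are a weak substitute.

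**Working it through.** **Inputs.** The equation, MET bands and validity rules come from Objectively-measured physical activity. The age range of 10 to 14 years comes from Participants, the game intensity from Feasibility studies, and 30 minutes of active play per day from the hypothesis at the end of Background.

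**The plan's own figure.** The sample size of 330 is built on BMI: 2 × (1.960 + 1.282)² × (2.0/0.8)² = 131.4, so 132 per arm; 132/0.8 = 165 per arm, 330 in total. It reproduces, but no power is stated for any accelerometer outcome, so it does not bear on this point.

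**Step 1: METs at zero counts.** With counts set to 0 the equation reduces to 2.757 − 0.08957 × age. The counts per minute needed to reach m METs are (m − METs at zero) / (0.0015 − 0.000038 × age).

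| Age | METs at 0 counts | Counts/min for 3 METs | Counts/min for 6 METs |
|---|---|---|---|
| 10 | 1.861 | 1017 | 3695 |
| 11 | 1.772 | 1135 | 3908 |
| 12 | 1.682 | 1262 | 4136 |
| 13 | 1.593 | 1399 | 4381 |
| 14 | 1.503 | 1547 | 4646 |

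Every value in the second column is above 1.5.

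**Step 2: where this stops.** Zero counts fall below 1.5 METs only above age (2.757 − 1.5)/0.08957 = 14.03 years. Beyond that the light threshold is low: 44 counts/min at 14.5 and 92 at 14.99. The article does not say whether age enters in whole or decimal years. In whole years, every visit at age 14 or younger is affected. In decimal years, visits after 14.03 are partly spared.

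**Step 3: what the sum becomes.** For any one child, sedentary + light + moderate + vigorous minutes = valid minutes. Up to age 14.03 the sedentary term (below 1.5 METs) is zero, so light + moderate + vigorous = valid minutes.

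- Swap 30 valid minutes a day of sitting for play recorded at 3 METs or more. Light time falls by 30 and moderate plus vigorous time rises by 30. The sum changes by 0.
- Wear the monitor 30 valid minutes longer while sitting. The sum rises by 30 and moderate plus vigorous time by 0.

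There is one exception. If unbroken zeros count as missing, sitting still for 20 minutes or more is removed as non-valid, and replacing it with play would raise the sum. That rise comes through the validity rule and cannot be told apart from longer wear.

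**Step 4: what does discriminate.** The 3 MET cut lies at 1017 to 1547 counts/min for ages 10 to 14, well clear of zero, so time at 3 METs or more separates sitting from activity. The laboratory range of 3.2 to 6.8 METs lies wholly above 3 but straddles 6, so a gain could be divided between the two separate tertiary outcomes.

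**The case against.** Five points can be made for the plan as it stands.

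- **Moderate and vigorous activity is measured.** A reader might infer from the secondary list that no outcome captures it. That is wrong: both bands are tertiary outcomes. The complaint is about rank and the unnamed sum, not about missing data.
- **The intended swap is sedentary to active, which a light-to-vigorous total should capture.** This would be a good answer if sedentary minutes lay outside the total. Step 3 shows that, for nearly the whole age range, they do not.
- **The pilot used time in all physical activities and saw a difference.** Continuity with the pilot is a fair reason to keep the measure, though not to make it the only accelerometer secondary outcome.
- **Laboratory METs are not METs predicted from a hip monitor.** This stands. Background says play may use arms, legs or the whole body, and the documents do not show that arm-led play registers at 3 METs or more on the right hip.
- **Changing a secondary outcome during an open trial invites suspicion of selection.** This also stands, and it governs how the change should be made.

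A reader might also infer that the pooled outcome has low power and that a false null is likely. The documents do not support a figure. Suppose the SD of the sum is 53.9 to 84.0 min/day (an assumption) with 132 per arm, so that SE = SD × √(2/132) = 6.63 to 10.34. An assumed gain of 15 min/day then has about 62% to 31% power. A gain equal to the hypothesised 30 minutes of play has about 99% to 83%. The answer depends on the assumed inputs, and both calculations treat sedentary minutes as outside the sum, which the equation contradicts.

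**Conclusion.** The concern holds as a mismatch between the ranked outcome and the behaviour promoted, made worse by the equation. Up to age 14.03 every valid minute scores at least 1.5 METs, so the light-to-vigorous sum equals valid wear time. Above that age it falls short only by minutes with very low counts. Within valid minutes, the expected effect of swapping inactive for active play is zero at those ages, whatever the SD. A difference in wear between arms would pass straight into the outcome.

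This rests on the equation and bands being applied as printed. It does not rest on any assumed SD or effect size, and no loss of power can be quantified from the documents. The primary BMI outcome is unaffected, and the moderate and vigorous tertiary outcomes remain usable.

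**What to change.** In Outcomes, make average daily time at 3 METs or more (moderate plus vigorous) the accelerometer secondary outcome. Move the light-to-vigorous sum to the tertiary list, beside the separate bands. Record this as a dated change made before any outcome data are analysed by arm, giving the zero-count arithmetic as the reason.

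The cost is outcome wording and one derived variable from data already planned. There are three downsides:

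- the pilot's all-activities measure becomes tertiary;
- a secondary outcome changes during an open trial, which the date and stated reason mitigate but do not remove;
- arm-led play may be under-recorded at the hip, so some real gain could score below 3 METs. The separate light band does not solve this, because it also contains sitting.
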